#### Participant timeline {13}

The assessments and interventions required at screening, randomisation, and follow-up visits are outlined in Table 2. Eligible patients will be randomised using the secure randomisation website, Sealed Envelope® (www.sealedenvelope.com), which generates anonymised kit codes for trial staff to identify the correct trial medication for the patient, whilst maintaining blinding. Patients should start taking the trial medication as close as possible to the randomisation date (for those enrolled as outpatients) or as soon as they are well enough after discharge from the hospital (for those enrolled as inpatients). Follow-up visits by contact at the outpatient appointment will be on day 10, then at outpatient appointments or by telephone at month 1 and 3-monthly thereafter for 18 months. At month 19, there will be an end-of-study safety telephone call as this marks the end of the treatment period for the trial and denotes the minimum follow-up period. Patients that finish the treatment period prior to the end of the trial will be followed up 6-monthly until the end of the trial.

**Table 2 Tab2:** Trial schedule of interventions and assessments

Visit number	Visit 1		Visit 2	Visit 3	Visit 4	Visit 5	Visit 6	Visit 7	Visit 8	Visit 9	Safety call	Long term follow-up
	(< 12 weeks from randomisation)	Month 0	Day 10	Month 1	Month 3	Month 6	Month 9	Month 12	Month 15	Month 18	Month 19	Every 6 months from month 24 to the end of the trial
	Screening	Randomisation	Follow-up									
Eligibility screening	X											
Informed consent	X											
Medical history	X											
Pregnancy test (*if applicable*)	X^a^											
Ascitic fluid analysis	X^b^											X
Blood tests, liver and renal function tests^c^	X		X^e^		X	X	X	X	X	X		X
Randomisation		X										
Adverse events review			X	X	X	X	X	X	X	X	X	X
Hospital admission review			X	X	X	X	X	X	X	X		X
Concomitant medication review	X		X		X	X	X	X	X	X		X
MARS Questionnaire					X	X	X	X	X	X		
EQ-5D-5L Questionnaire		X				X		X		X		
Dispense trial medication^d^		X			X	X	X	X	X			

^a^Pregnancy test must be completed within 2 weeks prior to randomisation

^b^Ascitic fluid analysis can be done within 12 weeks prior to randomisation

^c^Blood tests should include full blood count, with haemoglobin, white cell count, platelets, INR (or prothrombin time converted to INR), sodium, potassium, serum creatinine, and urea. Liver function tests should include albumin, alanine aminotransferase (ALT), alkaline phosphatase, and bilirubin. Renal function tests including eGFR

^d^At each indicated visit, one bottle of 100 capsules of trial medication is dispensed to the patient (either co-trimoxazole or placebo capsules)

^e^Visit 2 is to monitor the safety of the patient and to make any dose modifications to concomitant medications if needed

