### Eligibility criteria {10}

The inclusion and exclusion criteria for patient eligibility are listed in Table 1.

**Table 1 Tab1:** Eligibility criteria for ASEPTIC trial

Inclusion criteria	Exclusion criteria
Patients with cirrhosis of Child–Pugh class B or C and the presence of ascites requiring any diuretic treatment or at least one or more paracentesis within 3 months prior to enrolment	Patients with current or previous SBP (defined as ascitic polymorphonuclear count > 250 cells/mm^3^ with either positive or negative ascitic fluid culture without an evident intra-abdominal surgically treatable source of infection; a white cell count > 500 cell/mm^3^ or positive microbial culture may be considered as evidence of previous SBP if the site PI considers this was in the context of a likely clinical diagnosis of SBP)
At least 18 years of age	Patients receiving palliative care with an expected life expectancy of < 8 weeks
Documented informed consent to participate	Allergy to co-trimoxazole, trimethoprim, or sulphonamides
	Pregnant or lactating mothers
	Patient enrolled in a clinical trial of investigational medicinal products (IMPs) that would impact their participation in the study
	Patients with serum potassium > 5.5 mmol/L related to pre-existing kidney disease which cannot be reduced^a^
	Patients receiving antibiotic prophylaxis (except rifaximin)^a^
	Patients with long-term ascite drains^a^
	Women of child-bearing potential and males with a partner of child-bearing potential without effective contraception for the duration of the trial treatment
	Patients with pathological blood count changes^a^: haemoglobin < 70 g/L, granulocytopaenia defined as absolute neutrophil count < 500 cells/µL, and/or severe thrombocytopaenia with platelets < 30 × 10^9^/L
	Patients with severe renal impairment, with eGFR < 15 mL/min
	Patients with skin conditions: exudative erythema multiforme, Stevens-Johnson syndrome, toxic epidermal necrolysis, and drug eruption with eosinophilia and systemic symptoms
	Patients with congenital conditions: congenital glucose-6-phosphate dehydrogenase deficiency of the erythrocytes and haemoglobin anomalies such as Hb Köln and Hb Zürich
	Patients with acute porphyria
	Any clinical condition which the investigator considers would make the patient unsuitable for the trial

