^a^It is common for these investigations to change in patients with cirrhosis, and long-term ascitic drains may be removed. Patients may be rescreened for eligibility if this occurs

Originally, ascitic protein < 2 g/dL was proposed as an inclusion criterion for this trial; however, in the pilot phase, we found a low number of cases of low ascitic protein (38 out of 224 patients), despite only screening patients with refractory ascites and advanced liver disease. Also, there are no large-scale UK data concerning ascitic protein values and the use of ascitic protein in stratifying SBP risk remains contentious [13, 14]. Since it is well recognised that all patients with cirrhotic ascites are at high risk of bacterial infection, it was decided to change the inclusion criteria to persistent ascites without the need for an ascitic protein level. The intention of this amendment was to both increase the number of eligible patients for recruitment and still include patients at the greatest risk of SBP mortality. At the time of this amendment, 15 patients had been recruited. Sub-group analysis will be performed to examine the outcomes in patients with an ascitic protein content ≥ and < 2 g/dL.

The original eligibility requirement regarding the presence of ascites included the condition “despite 3 months of standard treatment”. Feedback from our sites described this time period requisite as a significant limitation to recruitment, and this was formally amended to “patients with cirrhosis of Child–Pugh class B or C and the presence of ascites requiring any diuretic treatment or at least one or more paracentesis within 3 months prior to enrolment”. This enables the recruitment of patients hospitalised with ascites shortly prior to their discharge.

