### Additional consent provisions for collections and use of participant data and biological specimens {26b}

Eligible patients who give their written informed consent will be investigated with baseline blood tests, ascitic fluid sample for white cell count and/or protein level, and pregnancy test if applicable.

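### Baseline ascitic fluid may lack either the cell count behind the SBP exclusion or the protein behind a planned subgroup, and qualifying results may be up to 12 weeks old at dispensing

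*Protocol article*

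**What the plan says.** **Content of the fluid sample.** The only statement of what is measured in the baseline fluid is in section {26b}, which asks for an "ascitic fluid sample for white cell count and/or protein level". The fluid row of Table 2 does not specify the tests. Table 1 excludes "Patients with current or previous SBP (defined as ascitic polymorphonuclear count > 250 cells/mm^3", with further wording on culture and on evidence of past episodes. Sections {10} and {20b} both plan a subgroup analysis split at an ascitic protein of 2 g/dL.

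**Timing.** Table 2 (section {13}) heads the screening visit "< 12 weeks from randomisation". Footnote b adds: "Ascitic fluid analysis can be done within 12 weeks prior to randomisation". One entry test has a shorter window, in footnote a: "Pregnancy test must be completed within 2 weeks prior to randomisation". The row "Blood tests, liver and renal function tests" is blank at Month 0, and the row "Dispense trial medication" has its first mark there.

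**Stability of the values.** The footnote to Table 1, which is attached to the potassium and blood-count exclusions among others, says: "It is common for these investigations to change in patients with cirrhosis". It goes on to allow rescreening.

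**The concern.** The SBP exclusion does two jobs. It keeps out patients who need treatment for a current infection, and it makes the secondary outcome, time to first SBP, a measure of new disease. If the required fluid test need not include a cell count, neither job rests on a measurement. The same loose wording lets a site omit the protein, and a planned subgroup then loses patients according to which test was requested.

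The timing raises a related question. The laboratory exclusions concern values that the article itself calls changeable, yet the qualifying result may be nearly 12 weeks old when the first bottle is dispensed. Two of those exclusion limits are also limits at which section {11b} stops the trial drug.

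**Working it through.** The plan states no figure on this point, so there is none to reproduce. The check sets the sections side by side and adds some short arithmetic.

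**1. What each permitted sample supplies**

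| Sample | Meets {26b}? | Count for the SBP exclusion? | Protein for the subgroup? |
|---|---|---|---|
| Protein only | yes | no | yes |
| Cell count only | yes | yes | no |
| Both | yes | yes | yes |

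Two of the three compliant forms leave a gap.

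**2. Table 2 read by column**

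- Eligibility screening: Visit 1 only.
- Bloods: Visit 1, day 10, months 3, 6, 9, 12, 15 and 18, then long-term follow-up.
- Fluid: Visit 1, then long-term follow-up (from month 24).
- Dispensing: Month 0, then months 3, 6, 9, 12 and 15.

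So no bloods or fluid are scheduled between Visit 1 and first dispensing.

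**3. Longest interval**

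- 12 weeks × 7 = 84 days. Fluid may be 84 days old at randomisation; bloods must be just under that.
- Taking day 10 from randomisation, the two scheduled blood tests are at most about 84 + 10 = 94 days apart. Of this, at most about 10 days are on drug.

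**4. Entry limits against on-treatment limits**

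| Value | Table 1 excludes | Section {11b} stops the drug |
|---|---|---|
| eGFR | < 15 mL/min | < 15 mL/min |
| Platelets | < 30 × 10^9/L | < 30 × 10^9/L without bleeding (< 50 with active bleeding) |
| Potassium | > 5.5 mmol/L, if due to kidney disease and not reducible | ≥ 6 mmol/L |

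The first two rows share a limit. Potassium does not, and a raised potassium alone does not exclude. The Table 1 footnote covers potassium and blood counts but not eGFR; section {11b} itself provides for eGFR falling and recovering.

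**5. Is 12 weeks long in this population?** This is an illustration only, from the control survival in section {14}: 66% at 18 months, exponential.

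- Monthly hazard = −ln(0.66)/18 = 0.0231.
- Deaths in 84 days (2.76 months): 1 − exp(−0.0231 × 2.76) = 6.2%.
- Deaths in 14 days (0.46 months): 1 − exp(−0.0231 × 0.46) = 1.1%.

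Clinical status can therefore change materially within the window. These are death rates, not rates of crossing a laboratory limit; the documents give none of the latter.

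**6. MELD.** The outcome in section {12} runs from baseline to the end of follow-up, which is 18 to 48 months (78 to 208 weeks). Baseline is not defined. Its components are scheduled before randomisation only at Visit 1, so that source is inferred. The largest share of the measured change that precedes randomisation is:

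- 18 months of follow-up: 12/(78 + 12) = 13%.
- 48 months of follow-up: 12/(208 + 12) = 5%.

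**7. Protein subgroup.** If a fraction m of patients lack a protein result, evenly across groups, the standard error of the interaction grows by 1/√(1 − m). As assumed values, m = 0.1 gives 1.05 and m = 0.5 gives 1.41. The documents support no particular m.

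**The case against.** The strongest reply is that exclusions describe the patient, not a dated laboratory result. Section {13} randomises eligible patients. Section {16c} makes the site investigator or delegate responsible for confirming eligibility and prescribing. Section {11d} adds a judgement on renal and potassium risk, and Table 1 ends with a general investigator exclusion. Twelve weeks is a ceiling, and inpatients recruited near discharge may well have fresh results. Day 10 bloods exist for safety, and the section {11b} rules then apply. The full protocol, not shown, may say more about rechecking. All of this stands, and it limits the timing issue to changes that nobody has detected.

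It can also be said that the protein requirement was deliberately dropped from eligibility, which may explain the wording in {26b}. That explains why protein is not an entry criterion. It does not explain why a planned subgroup factor is optional, or why the cell count is.

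Several stronger readings are tempting but not supported:

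- *Patients past an exclusion limit are randomised and given drug.* The article does not say so; a patient known to be past a limit is ineligible.
- *The 8-week life-expectancy exclusion conflicts with a 12-week window.* That criterion applies to patients receiving palliative care and is a clinical prognosis, so there is no conflict.
- *Prevalent SBP is counted as incident.* This needs SBP present at entry, missed clinically and diagnosed later. It is possible, but no frequency is given.
- *Old MELD values bias the comparison.* They affect both randomised arms alike, and section {20a} adjusts continuous outcomes for baseline. The result is noise.
- *The pilot's 38 of 224 with low protein gives the subgroup's size.* That screening was limited to refractory ascites and advanced disease, and the criteria have since been broadened.

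**Conclusion.** The point holds on two counts, of unequal strength.

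First, the wording in {26b} does not secure the measurement on which the SBP exclusion is defined, nor the factor for the protein subgroup. This follows directly from the text. What is exposed is the entry exclusion, one secondary outcome and one subgroup analysis. The number of patients affected is unknown.

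Second, Table 2 permits qualifying results up to 12 weeks old with none scheduled at Month 0, while the Table 1 footnote says that potassium and blood counts commonly change and section {11b} stops the drug at two of the entry limits. An undetected change past a limit at dispensing is therefore possible. Its rate cannot be calculated, and the next scheduled bloods come at day 10.

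The MELD effect is added noise in both arms, on at most 5% to 13% of the measured interval. This assumes that baseline MELD is the Visit 1 value. Nothing here biases the randomised comparison of overall survival.

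**What to change.** 1. In section {26b}, change *and/or* to *and*, so that every baseline fluid sample has both a cell count and a protein level, and name the count in the terms that Table 1 uses. The cost is one added routine assay on fluid already taken.
2. Reconcile Table 1, its footnote, section {11b} and Table 2 on how current the qualifying results must be at randomisation. The window and any resulting clinical rule are for the sponsor to set. The cost is a minor amendment, plus whatever repeat testing or late screen failures the chosen rule brings.
3. Define baseline MELD as the last value before randomisation, using recent routine results where they exist. This needs no extra visit.

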#### Sample size {14}

For overall survival as the primary outcome, we anticipate a hazard ratio (HR) of 0.62 and calculated that 432 patients will be required to generate 187 events, incorporating a 10% cumulative probability of loss-to-follow-up by the end of the study. Guided by the Kaplan–Meier 18-month survival estimate amongst patients with cirrhosis and ascites in the control arm of the ANSWER trial [30], and assuming an exponential survival distribution, we anticipate 66% survival in the control arm at 18 months. In the experimental arm, we expect 77% of patients surviving at 18 months. The recruitment will be uniform over a period of 2.5 years, and the follow-up time will be 18 months minimum with a maximum potential follow-up of 48 months. This calculation was based on a two-sided 5% type 1 error rate and 90% power. The primary event rate overall (blinded to allocation) will be monitored by the trial steering committee, and follow-up may be extended beyond the planned period to achieve the required number of events, with any extension agreed with the funder. Disruption to the trial schedule owing to the COVID-19 pandemic may necessitate an extension of the recruitment period.

#### Recruitment {15}

Both outpatients and inpatients will be recruited from at least 30 secondary or tertiary NHS hospitals that frequently manage patients with advanced liver disease. Outpatients will be screened when attending hepatology or liver transplant waiting list clinic appointments, or day case units for elective ascitic paracentesis. The recruitment period will be 30 months.

### Assignment of interventions: allocation

#### Sequence generation {16a}

The independent, online, computer-generated randomisation service, Sealed Envelope® (www.sealedenvelope.com), will be used to minimise allocation bias. Randomisation will use a minimisation algorithm incorporating a random element, stratifying by active participation on the liver transplant waiting list, rifaximin prescription at enrolment, and centre. To ensure a maximum balance is achieved across the stratification factors, minimisation will be carried out on these factors separately. In mid-2022, we submitted an amendment to include alcohol as a significant cause of cirrhosis and active alcohol consumption at randomisation as stratification variables following review by our oversight committees.

#### Concealment mechanism {16b}

The Sealed Envelope® software allows concealed allocation. A single labelled bottle with a unique kit code of the IMP will be dispensed following randomisation and at each subsequent 3-monthly follow-up visit.

#### Implementation {16c}

The responsibility for confirming patient eligibility and prescribing the IMP lies with the site PI or delegated clinicians. Eligibility decisions will be made in line with the approved protocol. Other clinicians employed at the same clinical site (including trial nurses who are registered independent prescribers) may enrol and prescribe trial treatments to patients only if they have received appropriate training on the trial and appear on the trial delegation log, approved by the PI.

### Assignment of interventions: blinding

#### Who will be blinded {17a}

Trial patients and all trial staff including clinicians and dispensing pharmacists will be blinded. The co-trimoxazole and placebo capsules will appear identical.

#### Procedure for unblinding {17b}

There will be no unblinding unless considered important for the patient’s care as assessed by the attending clinicians. If emergency unblinding is deemed necessary, this can occur at any time through, Sealed Envelope®.

### Data collection and management

#### Plans for assessment and collection of outcomes {18a}

Each patient will be given a unique trial patient identification number (PIN). Data will be collected using paper case report forms (CRFs) and will also be entered directly into an electronic data capture database (InferMed MACRO). Clinical outcomes will be logged by the trial staff. Validated questionnaires (e.g. MARS and EQ-5D-5L) will be used to collect data on certain outcomes.

#### Plans to promote participant retention and complete follow-up {18b}

The trial follow-up is designed to align with regular clinical follow-up appointments to minimise the additional burden for participants thus promoting retention. Patients that finish the treatment period prior to the end of the trial will be followed up 6-monthly until the end of the trial.

#### Data management {19}

Identification, screening, and enrolment logs will be kept at each trial site in a locked cabinet in a secured room and/or electronically. Electronic data will be stored on secure servers based at the lead organisation. The database will be password-protected and only accessible to specified trial members. After completion of the trial, these logs will be archived and stored securely by the sites for a minimum of 5 years. All data will be handled in accordance with the Data Protection Act 2018.

#### Confidentiality {27}

All data will be handled in accordance with the Data Protection Act 2018.

#### Plans for collection, laboratory evaluation, and storage of biological specimens for genetic or molecular analysis in this trial/future use {33}

Not applicable as no biological specimens for genetic or molecular analysis will be collected as part of this trial.

## Statistical methods

### Statistical methods for primary and secondary outcomes {20a}

A detailed statistical analysis plan will be written prior to the first unblinded analysis and approved in advance by the trial steering committee. The main analyses will be conducted following the intention-to-treat principle. For the primary outcome, Kaplan–Meier survival curves will be compared using the log-rank test, according to the allocated treatment in an intention-to-treat manner. An unadjusted Cox proportional hazards model will be fitted, and the unadjusted hazard ratio and 95% confidence interval will be presented. An adjusted Cox model will then be fitted, adjusting for the stratification factors (active participation on the liver transplant waiting list, rifaximin prescription at enrolment, alcohol as a cause of cirrhosis, and active alcohol consumption at randomisation if the amendment submitted in June 2022 is successful) by including them as covariates in the model. All statistical tests will use a two-sided *p*-value of 0.05.

If there is evidence of non-proportional hazards, the life expectancy difference and life expectancy ratio between the two arms will be presented [36]. The stratified log-rank test will be reported in this instance as well, and the odds ratio for death at 18 months will be calculated using logistic regression.

Binary secondary outcomes will be analysed using logistic regression, and continuous outcomes using linear regression adjusting for baseline values (i.e. ANCOVA). Time to the first incidence of SBP will be presented with Kaplan–Meier curves and compared between the arms using the log-rank test. Serious adverse event rates will be presented by treatment arm and grade. Quality of life scores will be compared using a hierarchical linear regression model.

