### Trial design {8}

This is a multicentre, randomised, phase 3a, placebo-controlled, double-blind clinical trial. The trial design is displayed in Fig. 1. Patients with cirrhosis and ascites receiving care from at least 30 NHS hospital specialist liver services will be screened using the inclusion and exclusion criteria. We plan to recruit 432 eligible consenting patients that will be allocated in a 1:1 ratio to receive either co-trimoxazole or an identical placebo for 18 months, with a 3-monthly follow-up during this period. Thereafter, post-treatment follow-up will be 6-monthly until the end of the trial, and the maximum possible trial duration for any individual is 48 months.

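### Treatment stops at 18 months while deaths count to 48 months, yet the survival measures that do not need proportional hazards are reported only if the data show non-proportionality

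*Protocol article*

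**What the plan says.** All the analysis wording is in the protocol article, Statistical methods for primary and secondary outcomes {20a}.

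- **Unconditional analyses.** "For the primary outcome, Kaplan–Meier survival curves will be compared using the log-rank test". Also: "An unadjusted Cox proportional hazards model will be fitted, and the unadjusted hazard ratio and 95% confidence interval will be presented". A Cox model adjusted for the stratification factors follows.
- **Conditional additions.** "If there is evidence of non-proportional hazards, the life expectancy difference and life expectancy ratio between the two arms will be presented". Then: "The stratified log-rank test will be reported in this instance as well, and the odds ratio for death at 18 months will be calculated" by logistic regression.
- **Timing of the SAP.** "A detailed statistical analysis plan will be written prior to the first unblinded analysis". The article gives no test or threshold for what counts as evidence.

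The design sections matter here too. Under Trial design {8}, patients are "allocated in a 1:1 ratio to receive either co-trimoxazole or an identical placebo for 18 months". Sample size {14} sets follow-up at 18 months minimum and 48 months maximum, and Outcomes {12} counts survival over all of it. Explanation for the choice of comparators {6b} lists waning efficacy among the questions the 18-month treatment period is meant to answer.

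**The concern.** A proportional hazards model assumes that the relative effect of allocation is the same throughout follow-up. Here every patient is due to stop the study drug at month 18 and may then be followed for up to 30 more months. A preventive effect that fades once the drug stops is an obvious possibility, and one the protocol names. The measures that stay interpretable in that case, the life expectancy difference and ratio, are nevertheless held back until the data show a departure.

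At stake is the description of the result. If the effect ended with treatment and the departure went unrecognised, the trial would put one averaged hazard ratio beside the curves. That figure would understate the on-treatment effect, overstate the later one, and depend on how much follow-up fell on each side of month 18.

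Two details of the fallback add to this. A stratified log-rank test lets the baseline hazard differ between strata. Within each stratum it still compares the arms in the way that is most powerful when the hazard ratio is constant, so it does not respond to a treatment effect that changes over time. And plain logistic regression for death at 18 months has no direct place for a patient lost alive before then.

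**Working it through.** **Inputs (Sample size {14} unless stated).** 432 patients, 1:1 (Trial design {8}); control survival 66% at 18 months, exponential; HR 0.62; uniform accrual over 30 months; follow-up 18 to 48 months; 10% cumulative loss, taken as exponential to month 48 and unrelated to prognosis; two-sided 5% and 90% power.

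**1. The plan's own figure.** Schoenfeld: events = 4(1.960 + 1.282)² / (ln 0.62)² = 184. Freedman gives 191. The stated 187 lies between them. The monthly control hazard is −ln(0.66)/18 = 0.02308 and the loss hazard is −ln(0.9)/48 = 0.00220. Averaged over uniform accrual, the probability of an observed death is 0.433, and 432 × 0.433 = 187. The design is reproduced.

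**2. Deaths if the effect ends at month 18 (assumption: HR 0.62, then 1).** With 216 patients per arm:

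| | to month 18 | after month 18 |
|---|---|---|
| Control | 72.1 | 37.4 |
| Co-trimoxazole | 48.1 | 43.8 |
| Total | 120 | 81 |

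**3. Chance of detecting the change.** The two log hazard ratios differ by −ln 0.62 = 0.478. SE = √(4/120 + 4/81) = 0.288. z = 0.478/0.288 = 1.66. Power of a two-sided 5% test = P(Z > 1.96 − 1.66) = 0.38. This test is told the correct change point. In 8,000 simulated trials a general score test of proportionality rejected in 28%.

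**4. The single hazard ratio.** Weighting by deaths: exp[(120/201) × ln 0.62 + (81/201) × 0] = 0.75. The simulation mean is also 0.75. The ratio of overall death rates per person-month is slightly higher, at 0.76.

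**5. Type I error and power (same simulation).**

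| Scenario | Log-rank | Restricted mean to 45 months | Log-rank, switching to restricted mean if the proportionality test rejects |
|---|---|---|---|
| No effect | 5.0% | 5.2% | 5.1% |
| HR 0.62 throughout | 91% | 91% | 91% |
| HR 0.62 to month 18, then 1 | 52% | 57% | 55% |

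The last column is a rule the protocol does not state. Even so, it would leave type I error near 5%.

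**6. The 18-month odds ratio.** Minimum follow-up equals the time point, so nobody is administratively censored before it. Loss by month 18, ignoring deaths, is 1 − 0.9^(18/48) = 3.9%. Lost while still alive: 3.2% control and 3.4% co-trimoxazole, about 14 patients in all. If the whole 10% were lost by month 18 (assumption), these become 8.2% and 8.8%.

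- True odds ratio: (0.2271/0.7729) / (0.34/0.66) = 0.570.
- Lost patients dropped: 0.570 under either loss assumption.
- Lost patients counted as alive: 0.572, or 0.575 with early loss.
- Assumed differential loss of 5% in one arm and 15% in the other: 0.536 to 0.618, depending on direction and handling.

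**The case against.** The strongest reply is that nothing is switched. The log-rank test, both Cox models and the Kaplan–Meier curves are produced whatever the data show, and the fallback only adds output. That is correct. A reader might infer that the choice of primary analysis depends on a preliminary test and that type I error suffers. The text does not say so, and the simulation shows no material inflation even under a switching rule. The curves would also let a careful reader see convergence after month 18.

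Second, the article does not prescribe a significance test as the trigger. Plots or the known end of treatment could count as evidence, and the criterion is proper SAP detail. So the 38% illustrates one plausible trigger and is not a property of the plan. What remains is that the reporting condition itself is fixed in the article, although the need for these measures can be foreseen.

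Third, an averaged hazard ratio over all follow-up is a legitimate summary for a treatment policy estimand, and an effect ending exactly at month 18 is only one scenario. Both points stand. They are reasons to keep the hazard ratio, not reasons to report it alone.

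Fourth, stratification is not useless: it deals with baseline hazards that differ across strata, and the sentence follows a model adjusted for the stratification factors. But it does not answer a changing treatment effect. The measures that do, listed first in the same fallback, are the ones made conditional.

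Finally, a reader might infer that the logistic odds ratio is invalid because of censoring. With minimum follow-up equal to 18 months, the shift is at most 0.005 under balanced, non-informative loss. Only strongly differential loss moves it by about 0.05.

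**Conclusion.** The point holds as a modest, nearly free improvement to the supportive effect measures. Non-proportional hazards are foreseeable from the design, so the measures that cope with them should not wait for the data to reveal the problem.

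If the effect ended at month 18, an ideal 5% test would reveal it in about 38% of trials. In the remainder, the planned numbers would be hazard ratios (unadjusted and adjusted) of about 0.75, for true values of 0.62 and then 1. This rests on the sample-size assumptions, an abrupt end of effect at month 18, exponential non-informative loss, and a 5% test as the trigger, which the article does not state.

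The stratified log-rank test is misplaced as a response to a time-varying treatment effect. The odds ratio concern is minor: about 3% lost alive before month 18, up to about 9% if all loss is early. The documents support no finding of inflated type I error, of a switched primary analysis, or of an unusable 18-month analysis. The gain is mainly in description, since restricted mean survival raises power only from 52% to 57% in this scenario.

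**What to change.** In the SAP, and in the protocol wording at the next amendment:

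1. Keep the log-rank test and the Cox hazard ratio as the primary analysis.
2. Always report the restricted mean survival difference and ratio with 95% confidence intervals, whatever any test of proportionality shows. Do so at 18 months and at one later time fixed in advance. Month 36 is an example: under uniform accrual 12/30 = 40% of patients would have that much potential follow-up.
3. Do not present the stratified log-rank test as a response to non-proportional hazards. If it is wanted, label it as a sensitivity analysis that allows for the stratification factors.
4. As a minor improvement, give the Kaplan–Meier 18-month survival difference with its 95% confidence interval in place of, or beside, the odds ratio, so that patients lost before month 18 contribute the follow-up they have. Little numerical change is expected.
5. Hazard ratios for 0 to 18 months and after 18 months are optional. Label them descriptive, because the later one compares only patients who survived to month 18.

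The cost is a wording change and a few more lines of output. Sample size, data collection and the primary test are unaffected.
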